### Interim analyses {21b}

There is no planned interim analysis.

### Methods for additional analyses (e.g. subgroup analyses) {20b}

In subgroup analyses of time to clinical success stratified by clinically relevant parameters (e.g. the size of WON, the proportion of necrotic components in the WON cavity [estimated and classified as < 30%, 30–60%, or > 60% [34], based on preprocedural CT findings], extension status of WON), we will assess statistical heterogeneity in the hazards by a specific variable by evaluating the Wald test on a cross-product of the variable and the treatment group in the Cox proportional hazards regression model. The multivariable Cox regression model will be used to adjust for potential imbalance of confounders and to calculate hazard ratios for clinical success comparing the immediate necrosectomy to the step-up approach.

### Methods in analysis to handle protocol non-adherence and any statistical methods to handle missing data {20c}

In the primary analyses of time to clinical success, patients who lose to follow-up will be treated as censored cases at the time of the last follow-up. In multivariable Cox regression models, we will assign a major category for missing data on categorical covariates and a mean or median value, as appropriate, for missing data on continuous covariates. We will confirm that excluding cases with missing data does not alter our findings substantially. In the analyses of the secondary endpoints, patients with missing data on the corresponding variable will be excluded.

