### Objectives {7}

The primary objective of the WONDER-01 trial is to evaluate the superiority of immediate DEN over drainage-oriented step-up approach following EUS-guided drainage of WON in terms of time to clinical success. The secondary objectives include assessments of a technical success rate, procedure-related adverse events, and long-term outcomes (detailed in Table 1).

**Table 1 Tab1:** The primary and secondary endpoints of the WONDER-01 trial

Primary endpoint	Secondary endpoints
Time from randomisation to clinical success^a^	Incidence of procedure-related adverse events graded by the AGREE classification [25] as well as the ASGE lexicon guideline [26]
Clinical success is defined as (1) a decrease in a WON size to 3 cm or less and (2) an improvement of at least two out of the three inflammatory markers (i.e. body temperature, white blood cell count, and C-reactive protein)	Mortality from any cause
	Technical success rate of the initial EUS-guided drainage
	Incidence of a biliary stricture and gastrointestinal obstruction
	Number of interventions
	Total procedure time
	Time requiring endoscopic and/or percutaneous drainage
	Length of hospitalisation
	Length of ICU stay
	Duration of antibiotics administration
	Total costs of interventions and hospitalisation
	Incidence of WON recurrence
	Time from clinical success to WON recurrence
	Incidence of a pancreatic pseudocyst
	Incidence of new-onset diabetes
	Incidence of clinical symptoms associated with pancreatic exocrine insufficiency
	Incidence of pancreatic cancer
	Incidence of sarcopenia
	Changes in the morphology and volume of the pancreas

^a^Patients who do not undergo clinical success within 6 months of the randomisation will be treated as cases with clinical failure

Abbreviations: *ASGE* American Society for Gastrointestinal Endoscopy, *EUS* Endoscopic ultrasound; *ICU*, Intensive care unit, *WON* Walled-off necrosis

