### Sample size {14}

For the sample size calculation, we assumed that the rates of clinical success at 60 days of the initial EUS-guided drainage were 60% in the immediate necrosectomy group and 35% in the step-up approach group according to preliminary data from a retrospective analysis by the WONDERFUL study group (under submission). When we planned 36 months for patient accrual and 6 months for follow-up, 64 patients were required with a two-sided α level of 0.05 and a power of 0.80. Taking the dropout into account, we planned a sample size of 70 patients (35 patients per arm).

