## Data collection and management

### Plans for assessment and collection of outcomes {18a}

Clinical parameters at baseline and outcome variables have been pre-defined. To promote the quality of data on the primary endpoint (i.e. clinical success), the expert panel will review the clinical course and CT images upon request. Data on those variables will be collected from the electronic medical chart at each centre. The schedule of enrolment, randomisation, interventions, and assessments is summarised in Table 3.

**Table 3 Tab3:** Schedule of interventions and assessments in the WONDER-01 trial

	Study period					
	Pre-intervention	Intervention (within 6 months of randomisation)				Post-intervention
	≤ 10 days before randomisation		Within 3 days of randomisation	7 days after intervention	Clinical success	After five years of clinical success
	Screening	Randomisation	Intervention		Assessment	Follow-up
Informed consent	X					
Eligibility screening	X					
Assessment of WON	X					
Assessment of symptoms	X				X	
Body temperature	X			X	X	
Blood test^a^	X			X	X	
Imaging study^b^	X			X^c^	X	
Electrocardiogram	X					
Randomisation		X				
Interventions			X			
Assessment of primary endpoint					X	
Assessment of secondary endpoints				X	X	X
Monitoring of adverse events				X	X	X

^a^A blood test includes the following items: white blood cell count, haemoglobin, platelet count, albumin, aspartate aminotransferase, alanine aminotransferase, gamma-glutamyl transpeptidase, alkaline phosphatase, total bilirubin, amylase, lipase, blood urea nitrogen, creatinine, C-reactive protein, and international normalised ratio of prothrombin time

^b^Contrast-enhanced computed tomography is performed unless there are contraindications for contrast use. Magnetic resonance imaging may be performed on the investigator’s discretion

^c^Imaging studies are performed at least every 2–3 weeks during the intervention period

Abbreviation: *WON* Walled-off necrosis

The investigators at each centre will collect relevant patient data from the electronic medical chart and input anonymised data to the trial database. The standardised trial database has been constructed using the Microsoft Access software (Microsoft Corp., Tokyo, Japan) and has been distributed to participating centres. The database file will be uploaded to the online storage that can be accessed only by the investigators.

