## Statistical methods

### Statistical methods for primary and secondary outcomes {20a}

In the primary analysis, we will compare times to clinical success between the immediate necrosectomy and step-up approach groups. In our primary hypothesis testing, cumulative survival probabilities of times to clinical success will be estimated using the Kaplan–Meier product-limit method and be compared using the log-rank test. Patients are censored at the time-point of salvage surgery, the last follow-up, 6 months of the randomisation, or death, whichever came first. In the secondary analyses, we will use Student’s *t*-test or Wilcoxon rank-sum test, as appropriate, for continuous variables; the chi-square test or Fisher’s exact test, as appropriate, for categorical variables; and the log-rank test for time-to-event variables.

The two-sided α level of 0.05 was used for statistical significance for all analyses. All analyses will be conducted for the intention-to-treat population, and examinations of per-protocol population will represent secondary analyses.

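### All analyses are labelled intention-to-treat, yet randomised patients with a missing secondary outcome are excluded; for the long-term endpoints that exclusion can depend on response to treatment

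*Protocol article*

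**What the plan says.** On the analysis population, section {20a} of the protocol article states: "All analyses will be conducted for the intention-to-treat population, and examinations of per-protocol population will represent secondary analyses". There is no exception for secondary endpoints.

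On missing secondary outcomes, section {20c} states: "In the analyses of the secondary endpoints, patients with missing data on the corresponding variable will be excluded". No alternative method is given for them. The one sensitivity check in that section follows the sentence on missing Cox covariates, and it is itself a complete-case check.

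On timing, Table 3 in section {18a} marks assessment of secondary endpoints in three columns: 7 days after intervention, at clinical success, and "After five years of clinical success". The last two exist only for a patient who reaches clinical success.

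On definitions, Table 1 in section {7} lists 19 secondary endpoints. One is defined from success: "Time from clinical success to WON recurrence". The other long-term items (pseudocyst, new-onset diabetes, exocrine insufficiency symptoms, pancreatic cancer, sarcopenia, pancreatic morphology and volume) are not defined relative to success in Table 1.

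**The concern.** Removing a randomised patient because a post-randomisation outcome is missing leaves a subset of those randomised. Calling that comparison intention-to-treat tells the reader that randomisation protects it, when the protection holds only if missingness is unrelated to prognosis within each arm.

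For the long-term endpoints there is a specific reason to doubt this. If late data are collected as Table 3 schedules them, a patient who never reaches clinical success has no late assessment point, and section {20c} then removes that patient from the comparison. Clinical success is the outcome that the trial expects immediate necrosectomy to bring forward, so the patients left in could be selected differently in the two arms. Section {7} makes long-term outcomes a secondary objective, so these comparisons will be read and cited.

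**Working it through.** **Inputs.** Success at 60 days is "60% in the immediate necrosectomy group and 35% in the step-up approach group" (section {14}), with 35 patients per arm. Failure means no success within 6 months of randomisation (section {12}). I assume exponential times to success, 60 days counted from randomisation (the plan counts from drainage, which follows within 72 h), and no deaths or surgery.

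**Step 1: reproduce the plan's own figure.** The plan states "64 patients were required with a two-sided α level of 0.05 and a power of 0.80", with 36 months of accrual and 6 months of follow-up.
- Hazard ratio = ln(0.40)/ln(0.65) = 2.127.
- Freedman events = (1.960 + 0.842)² × (3.127/1.127)² = 60.4, rounded up to 61.
- Mean event probability with uniform accrual and follow-up to month 42 = 0.980, so N = 61/0.980 = 62.2, rounded up to 63.
- The Lachin–Foulkes exponential-rate formula gives 63.4, rounded up to 64, which is the plan's figure.
- 64/(1 − 6/70) = 70, so the implied dropout allowance is 6 of 70 (8.6%).

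The exponential reading therefore agrees with the plan's own calculation.

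**Step 2: patients without success at 6 months.**

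| | Immediate | Step-up | Step-up share |
|---|---|---|---|
| 180 days | 0.40³ = 6.4%; 2.2 of 35 | 0.65³ = 27.5%; 9.6 of 35 | 9.6/11.9 = 81% |
| 182.6 days | 6.1%; 2.2 of 35 | 26.9%; 9.4 of 35 | 81% |

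An endpoint collected only at success-anchored visits would compare about 33 v 25 to 26 patients, before any deaths or losses.

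**Step 3: does this show who will be missing?** It does not; these are failure rates. Suppose the 6 implied dropouts are unrelated to arm and response. Step-up non-responders are then 0.275/2 = 14% of those dropped (6-month status), or 0.65/2 = 32.5% (60-day status). They exceed half only if non-responders are missing k times as often as responders, where
- 6-month status: k = (2 − 0.064 − 0.275)/(0.275 − 0.064) = 7.9;
- 60-day status: k = (2 − 0.40 − 0.65)/(0.65 − 0.40) = 3.8.

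**Step 4: what exclusion could do to a success-anchored incidence.** Suppose every non-responder is excluded and, within each response group, risk is the same in both arms. Responders then show no difference. Over all randomised patients, step-up minus immediate is (0.275 − 0.064) × (non-responder risk − responder risk) = 0.21 × that gap. For gaps of −20, 0 and +20 percentage points (assumed), the hidden difference is −4.2, 0 and +4.2 points. With 35 per arm and risks near 23%, the standard error of a difference is √(2 × 0.23 × 0.77/35), or about 10 points. The sign depends on a gap that the article does not give.

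**The case against.** The strongest reply is that section {20a} names a population, patients as randomised with per-protocol secondary, and section {20c} says how missing values are handled within it. Available-case analysis by randomised arm is common, so on this view the conflict is one of labelling. Non-response is itself an observed result (clinical failure). Section {18b} asks all enrolled patients to attend at least monthly after discharge, imaging is repeated every 2–3 weeks during the intervention period, and missing data are queried and monitored. Section {20a} also gives log-rank tests for time-to-event secondary variables, which accommodate censoring. A patient whose collection never resolved is outside time to recurrence by definition, and is not a missing case.

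Much of this stands, and it limits the point. A reader might infer that under the plan's rates the excluded patients are mostly step-up non-responders. The 60% and 35% are success rates, and the article gives no missingness rate by arm, response or endpoint. A reader might also extend the concern to all 19 secondary endpoints. Nothing links non-response to missing data for mortality, adverse events, technical success, number of interventions, length of stay or costs, and exclusion is per variable.

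The reply does not remove the narrower point. Table 1 lists most long-term endpoints as incidences, so the log-rank provision does not clearly reach them. No sentence says that the monthly-visit data of patients without success enter those analyses. Section {20c} states a rule, so this is not a detail merely left to a fuller document.

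**Conclusion.** The concern holds in a limited form. Sections {20a} and {20c} conflict as written. For the long-term endpoints, the success-anchored schedule lets exclusion depend on treatment response. The group at risk of exclusion is about 2 v 9 to 10 of 35, about 81% of it step-up, given constant hazards extrapolated from one 60-day figure and no deaths or surgery.

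How many of these patients would really lack data is unknown, and so are the size and direction of bias. It might be inferred that the rule works against the better arm. That would require non-responders to have a higher long-term event risk, for which the article offers no figure. The illustrative 4.2 points is also small beside a standard error of about 10 points, so what is at stake is mainly correct labelling and interpretability. The primary analysis is unaffected, because patients lost to follow-up are censored there.

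**What to change.** - Reconcile sections {20a} and {20c}: reserve the intention-to-treat label for analyses that all randomised patients enter, and call the others available-case, with the number analysed in each arm.
- Analyse the long-term incidence endpoints that do not presuppose resolution (for example new-onset diabetes, exocrine insufficiency symptoms, pseudocyst and pancreatic cancer) in all randomised patients, as time from randomisation. Use follow-up already collected, censor at last contact, and treat death as a competing event.
- Keep the complete-case analysis as a sensitivity analysis.
- Label WON recurrence and time from clinical success to recurrence as descriptive results in patients who reached clinical success. Counting never-resolved patients as recurrence-free would favour the arm with more failures.
- Do not impute long-term outcomes from clinical-success status. If no non-responder has a value, the data cannot inform that term of the model.

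The cost is slightly more analysis work and changed wording, with no new patients. The downside is reliance on non-informative censoring for patients lost to follow-up. Patients without success may also contribute shorter follow-up, because the article does not say how long the monthly visits continue, so follow-up time should be reported by arm.

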### Plans to give access to the full protocol, participant-level data and statistical code {31c}

The full protocol and statistical code will be accessible to the public on reasonable request. There is no plan of granting public access to participant-level dataset. The results of the present trial will be presented at conferences/seminars and be published in a peer-reviewed journal to maximise the chances of dissemination of the results to the public. The results will also be posted in the trial registries, ClinicalTrials.gov, University Hospital Medical Information Network (UMIN), and Japan Registry of Clinical Trials (jRCT).

## Oversight and monitoring

### Composition of the coordinating centre and trial steering committee

The trial steering committee consists of the principal investigator ([name]), co-principal investigators ([name] and [name]), and the representative of the investigator team at each centre. The committee will hold an online meeting every 2–3 months to check the progress of the trial and share the information on severe adverse events (SAEs). The Clinical Research Support Centre at The University of Tokyo Hospital provides day-to-day organisational support for the trial which monitors an annual report of the trial progress and SAEs submitted by the principal investigator.

### Composition of the data monitoring committee, its role and reporting structure {21a}

The Data Monitoring Committee has a monitoring manager who independently oversees the progress of the trial and compliance with the protocol using pre-defined monitoring forms. The monitoring manager will check the information in the electronic medical charts and the trial database to confirm the appropriateness of enrolment, allocation, interventions, and follow-up as well as missing data for outcome evaluation. The monitoring manager will report to the principal investigator whether there is a deviation from the protocol. The monitoring will be done independent from the competing interests.

### Adverse event reporting and harms {22}

SAEs are defined as unfavourable events that cause patient death, life-threatening events, unexpected or prolonged hospitalisation, or permanent or severe disability, regardless of plausibility of causal associations with the trial interventions. All SAEs will be managed by treating investigators at each centre. Consulting with the treating investigators, the principal investigator will evaluate the plausibility of the causal association using the MEDDEV (MEDical DEVices Documents) guidelines 2.7/1 revision 4, proposed by European Commission [35]. In the case of SAEs, the investigators will submit a report to the principal investigator using a pre-defined form. Subsequently, the principal investigator will consult with the institutional review board and the director of The University of Tokyo Hospital for the continuation of the trial. The information on SAEs will be shared with participating investigators to ensure the safety of the trial interventions.

### Frequency and plans for auditing trial conduct {23}

No audit is planned in the present trial. The data will be monitored by the committee.

### Plans for communicating important protocol amendments to relevant parties (e.g. trial participants, ethical committees) {25}

We will submit any modifications of the protocol (e.g. changes to the eligibility criteria, participating centres, endpoints, analyses) to the institutional review board at each centre and obtain the approval. The information at the trial registries will be updated accordingly. Trial participants will be informed about the amendments approved by the institutional review boards.

### Dissemination plans {31a}

The results of the present trial will be presented at conferences/seminars and be published in a peer-reviewed journal to maximise chances of dissemination of the results to healthcare professionals and the public and to contribute to the improvement of public health. The results will also be posted in the trial registries, ClinicalTrials.gov, UMIN, and Japan Registry of Clinical Trials (jRCT). Plain language summaries of the findings will be shared with trial participants on request.

## Discussion

WONDER-01 has been designed as a multicentre RCT that aims to evaluate the efficacy and safety of the immediate DEN approach compared to the step-up approach in patients with WON receiving EUS-guided drainage. Our survey of expertise endoscopists demonstrated considerable heterogeneity in clinical practice of endoscopic treatment of WON, suggesting an urgent need for RCTs for standardisation of the treatment protocol in this setting. The promise of clinical effectiveness of immediate DEN following EUS-guided drainage of WON has been supported only by retrospective series. In a multicentre comparative study, DEN initiated during the same session of EUS-guided drainage appeared to associate with a smaller number of DEN without no substantial increase in the risk of adverse events [14]. These lines of evidence prompted us to design a RCT to investigate the potential of immediate necrosectomy in managing endoscopically treated WON effectively.

The WONDER-01 trial has strengths in addition to those of RCTs in general. First, enrolment of participants at multiple centres will likely ensure the generalisability of our findings; this strength is considerably important given the variations in clinical practice of adjunctive and supportive treatment during the periprocedural period of EUS-guided treatment of WON [19, 33]. In addition, the relative rarity of WON patients requiring interventions may hamper the timely enrolment of participants. To encourage the enrolment, the current trial will be conducted at 23 centres (as of November 2022), and additional centres will be recruited if required. Therefore, the trial will be completed within the planned accrual period if 2 to 3 participants are enrolled at each centre (approximately one participant annually). Second, the broad inclusion criteria have been set to ensure the representativeness of our participants as patients with large-size WON. Third, EUS-guided drainage of WON and subsequent interventions including DEN will be performed on an inpatient basis according to the local practice. The hospitalisation will allow us to evaluate adverse events accurately during the periprocedural period.

We acknowledge potential challenges of the current trial. First, there may be difficulties in accurately differentiating WON from other types of fluid collections such as pseudocysts. Nonetheless, we have set up the online meeting platform so that we can hold the expert panel consisting of multiple gastroenterologists and board radiologists and draw a mature conclusion on the eligibility in a timely fashion. Second, due to the nature of the interventions in the experimental and control groups, the participants and endoscopists cannot be blinded to the assigned groups. Yet our outcome evaluators and data analysists will be blinded to the assignment to mitigate a bias due to the open-label procedures.

The current clinical guidelines have no recommendation on the timing of DEN following EUS-guided drainage of WON since no clinical RCTs have examined the timing of DEN in this setting [4, 6, 36]. Therefore, the results of this large, multicentre RCT are expected to add to the literature and help us to implement evidence-based practice for better clinical outcomes of patients with WON.

